### Blinding assessment

To test the patient-blinding effects, all patients will be asked to guess their group assignment allocation within 2 min after the last treatment session at week 12 as following: “Which group do you think you are in?” A. traditional acupuncture; B. modified acupuncture; or C. not sure.

### Credibility and expectancy

Credibility and expectancy of patients will be assessed by a Likert-scale Credibility/Expectancy Questionnaire (see Table 2) before the first treatment.

**Table 2 Tab2:** Expectations for the efficacy of acupuncture are varied. If using following statements to describe your views on your disease/symptoms after the entire course of treatment, how much do you agree? For each statement, please choose the closest answer

	Strongly disagree	Disagree	Neutral	Agree	Strongly agree
a. My illness will get much better.	□_1_	□_2_	□_3_	□_4_	□_5_
b. I will face my disease better.	□_1_	□_2_	□_3_	□_4_	□_5_
c. Symptoms of my disease will disappear.	□_1_	□_2_	□_3_	□_4_	□_5_
d. I will be more vigorous than before.	□_1_	□_2_	□_3_	□_4_	□_5_

### Adverse events

AEs data will document the occurrence, duration, and severity of adverse reactions (symptoms and signs), and how the event was resolved (or not) during the treatment. Based on their potential association with the acupuncture needling procedure, AEs will be categorized by acupuncturists and related specialists as treatment-related or not within 24 h after occurrence. Common treatment-related AEs include local subcutaneous hematoma, itching at the sites of needle insertion, continuous post-needling pain, dizziness, and so on. All participants will receive routine blood test, liver function (alanine transaminase and aspartate transaminase), and kidney function tests (serum creatinine and blood urea nitrogen). These tests will be performed twice, after randomization and at the end of 12-week treatment period. Serious adverse events will be reported to Medical Ethics Committee and the participant will be treated with relevant conventional therapy or hospitalization if necessary (the participant’s allocated intervention will be revealed).

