**Methods/design:**

This is a study protocol for a randomized, placebo-controlled clinical trial. A total of 118 patients with DPN will be recruited and randomly assigned in a 1:1 ratio to either the MA group or SA group. All patients will receive 24 sessions over 12 weeks. Participants will complete the trial by visiting the research center at month 6 for a follow-up assessment. The primary outcome is peroneal motor nerve conduction velocity (peroneal MNCV) at week 12 compared with baseline. Secondary outcomes include peroneal motor nerve action potential amplitude (peroneal MNAP) and latent period (peroneal MNLP), sural sensory nerve conduction velocity (sural SNCV), action potential amplitude (sural SNAP) and latent period (sural SNLP), fasting plasma glucose (FPG), 2-h postprandial blood glucose (2hPG), glycated hemoglobin (HbAlc) at week 12 compared with baseline, Michigan Neuropathy Screening Instrument (MNSI) score and Diabetes Specific Quality of Life scale (DSQL) at week 12 and month 6 compared with baseline. Safety will be assessed during the whole trial. Masking effectiveness will be assessed by patients.

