## Background

Diabetic peripheral neuropathy (DPN) is the most common cause of neuropathy worldwide, and its prevalence increases with the duration of diabetes [1]. Approximately 50% of patients with diabetes will develop peripheral neuropathy [1–3]. DPN is symmetric and predominantly sensory, starting distally and gradually spreading proximally in a glove-and-stocking distribution [1]. DPN is associated with the development of foot problems such as foot ulcers and is one of the leading causes of amputations. The high-frequency underreport and undertreatment of DPN can lead to an increased risk for morbidity and mortality and decreased quality of life [1, 2]. Once symptoms appear, there are few effective therapeutic strategies [4]. While neuropathic pain and paresthesia can be palliated by anti-convulsant drugs, tricyclic antidepressant drugs, or serotonin-noradrenalin re-uptake inhibitors [5], pharmacological management of decreased sensation is generally ineffective. Therefore, more and more patients turn to seek non-pharmacological treatments. Multiple complementary and alternative medicine therapies such as acupuncture and yoga have shown efficacy in the treatment of painful peripheral neuropathy [6]. A pilot RCT has demonstrated practicality and feasibility of acupuncture as an additional well-tolerated treatment without appreciable side effects for people with DPN [7]. Acupuncture may effectively ameliorate selected DPN symptoms, such as aching pain, burning pain, prickling sensation, numbness, and allodynia in American Indian patients [8]. Reviews concerning acupuncture for peripheral neuropathy (PN) have found that, despite the majority of studies reporting positive results, a reliable statement of effectiveness is not possible due to methodological limitations such as unsuitable control group and blinding [9–11]. Also, inconsistency of outcome measures and lack of use of global neuropathy-specific patient-reported outcome measures have confounded results. Overall, the quality of acupuncture intervention delivered in individual studies was low. Appropriately powered RCTs with suitable control groups, validated and proper outcome measures for DPN patients, and more accurate reporting of acupuncture interventions, including point selection rationales, point locations, and practitioner qualifications, are needed. Therefore, we have designed a randomized, sham-controlled, participant-blinded and assessor-blinded study with a 6-month observation period to explore its effectiveness and safety.

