### Randomization and allocation concealment

All eligible patients will be randomly assigned to manual acupuncture (MA) group or sham acupuncture (SA) group in a 1:1 ratio. The blocked randomization sequence will be computer-generated (Excel) by an independent statistician, who will not be involved in implementation and statistical analysis of the trial. The allocation will be placed inside sequentially numbered sealed opaque envelopes which will be opened only after enrollment. The treatment allocation will be revealed to acupuncturists out of patients’ sight to ensure blinding. To reduce the risk of observer bias, the acupuncture practitioners will be discouraged from discussing treatments or previous results with patients. The random allocation sequence and sealed opaque envelopes will be kept separately by two specific researchers. The clinical research coordinator will be responsible for enrolling patients, obtaining informed consent, and requesting randomization.

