### Masking

Due to the nature of acupuncture, masking of acupuncturists is quite difficult to achieve. Patients, outcome assessors, and statisticians who perform the statistical analyses will be blinded to group assignment. The treatments subjects received will be not revealed until the statistical analysis is completed.

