A suitable control group is critical for a well-designed clinical trial. On the basis of literature review, using a blunt-tipped needle that does not penetrate the patient’s skin is the most commonly used approach for administering sham treatments among acupuncture trials [16, 17]. Patients who have received acupuncture treatment in the last 3 months and can distinguish SA from MA will be excluded. The same control group design, no skin penetration at acupoints, was adopted and succeeded in masking patients with DPN [7, 14, 15, 18]. Furthermore, all patients will be asked to guess which treatment they have received to test patient-blinding effects at week 12.

The change of nerve conduction velocity is chosen as the primary outcome because it is the highest sensitive and objective method to detect neuropathy. Multiple systematic reviews [11] recommended nerve conduction velocity as a main outcome, and it had been widely used as an outcome measure in DPN studies [23]. At the same time, assessment of the severity of DPN mainly depends on patient-reported outcomes. The MNSI is the most DPN-specific patient-reported measure. In this trial, we use the DSQL to evaluate quality of life in patients with DPN before and after acupuncture treatment. The DSQL captures the impact of detailed aspects of modern diabetes management (e.g., carbohydrate counting and flexible insulin dose adjustment) that is extensively used in evaluating quality of life in DM. The DSQL offers a valuable tool for assessing the impact of treatment approaches on QoL in adults with DM [20].

The limitation of our trial is acupuncturists are not blinded for the nature of intervention. We hope results of this trial will provide more reliable evidence and clarify the value of acupuncture as a treatment for DPN.

To summarize, this trial meets the methodological demand of adequate randomization and allocation concealment, blinding of patients, outcome assessors, and statisticians. Findings of this study will provide high-quality evidences for evaluating the efficacy and safety of acupuncture treatment for DPN.

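### Relatedness of adverse events is judged partly by acupuncturists who know the arm, and the adverse-event recording window is worded ambiguously against the promise of whole-trial safety assessment

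*Protocol article*

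**What the plan says.** **Attribution.** The Adverse events section sets the criterion, "Based on their potential association with the acupuncture needling procedure", and names who applies it: "AEs will be categorized by acupuncturists and related specialists as treatment-related or not within 24 h after occurrence". Under Randomization and allocation concealment, "The treatment allocation will be revealed to acupuncturists out of patients’ sight to ensure blinding". The Masking section concedes that "masking of acupuncturists is quite difficult to achieve" and lists three blinded roles: patients, outcome assessors and the analysing statisticians. The specialists who share the relatedness decision are not on that list. The Discussion repeats the point: "The limitation of our trial is acupuncturists are not blinded for the nature of intervention".

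**Window.** The Abstract (Methods/design) states "Safety will be assessed during the whole trial", and the Background describes a "study with a 6-month observation period to explore its effectiveness and safety". The Follow-up section adds 3 months after the 12 weeks of treatment. The one sentence on documenting adverse events ends "and how the event was resolved (or not) during the treatment". The safety laboratory tests are done twice, the second time when the 12-week treatment ends. The patient's own safety rating (Assessment of safety) is taken once, after those 12 weeks.

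**The concern.** Safety is a stated aim of the trial, alongside efficacy.

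The relatedness label is a judgement, and one of the two parties making it knows the arm. The criterion itself also follows the arm: sham involves no skin penetration, and the examples of related events include haematoma and itching where the needle went in. For an unspecific complaint such as dizziness, a rater who knows that no needle entered the skin has a reason to call it unrelated, while the same complaint after real needling is readily called related. Any comparison of related events would then partly reflect the rater's knowledge.

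The recording window is a separate matter. If recording ended with treatment, delayed events would fall outside it, and the whole-trial statement could not be met. The 24-hour attribution step also involves acupuncturists, who no longer treat the participants once the sessions have ended.

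**Working it through.** **1. Attribution: the sections side by side**

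- Who decides: acupuncturists and related specialists (Adverse events).
- What the acupuncturists know: the allocation (Randomization and allocation concealment; Masking; Discussion).
- What the specialists know: not stated. They are absent from the list of blinded roles (Masking).
- On what basis: association with needling (Adverse events). Real needling occurs only in the manual acupuncture arm (Sham acupuncture).

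The written rule therefore lets the label depend on the arm. Occurrence, duration and severity are documented separately from the label, so an event called unrelated stays on record. The bias is confined to the related/unrelated split.

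**2. Attribution: an illustration under assumptions**

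The document gives no adverse-event rate and no labelling probabilities, so the values below are assumed. The only input from the plan is the group size. It reproduces as 47 / (1 − 0.20) = 58.75, rounded up to 59 per group.

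Let a true proportion p of patients have an event, equal in both arms. Let the probability of the label related be a in the acupuncture arm and b in the sham arm.

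Expected related counts are 59 × p × a and 59 × p × b. The all-cause count is 59 × p in each arm.

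| p | all-cause, each arm | related, a = 0.8 vs b = 0.4 | related, a = 0.7 vs b = 0.5 |
|---|---|---|---|
| 0.10 | 5.9 | 4.7 vs 2.4 | 4.1 vs 3.0 |
| 0.20 | 11.8 | 9.4 vs 4.7 | 8.3 vs 5.9 |
| 0.30 | 17.7 | 14.2 vs 7.1 | 12.4 vs 8.9 |

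The ratio of related counts is a/b whatever p is: 0.8/0.4 = 2.0 or 0.7/0.5 = 1.4. A spurious excess of 40% to 100% appears although the true rates are equal, while the all-cause counts stay equal. This shows the mechanism. It does not estimate what will happen in this trial.

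**3. Window: the two readings**

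- Reading A: the closing phrase governs the whole sentence. Recording then covers the treatment period and conflicts with the Abstract and Background.
- Reading B: the phrase governs only how an event was resolved. The sentence then sets no end to recording, and there is no conflict.

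The surrounding text leans towards A without settling it. Every patient-level safety measure with a stated time ends at week 12. The Michigan Neuropathy Screening Instrument and the quality-of-life scale name month 6 explicitly, and the adverse-event text does not. The Follow-up section mentions no safety collection.

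**4. Window: size under reading A**

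- Treatment plus follow-up: 12 weeks = 2.76 months; 2.76 + 3 = 5.76 months; 3 / 5.76 = 52%.
- Counting month 6 as 26 weeks: (26 − 12) / 26 = 14 / 26 = 54%.

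These are shares of observation time after treatment, not shares of events lost.

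**The case against.** On the window, a reader might infer that adverse events are recorded only during treatment and that later harms are missed. The documents do not support that. No sentence says only, and the phrase can attach to the resolution of the event alone. The Abstract and Background both point to safety over the full observation period. Reporting of serious adverse events to the ethics committee has no stated end date, and the Data and Safety Monitoring Board reviews safety every 6 months. Fig. 3, where collection by visit would normally appear, is not visible and may show adverse events at follow-up. All of this stands, so the window point is a request to reconcile wording, with a conditional consequence. It does not remove the point: a board can review only what is collected, and the timed measures do stop at week 12.

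On attribution, acupuncturists do not decide alone, the specialists could in fact be blinded, and the lack of blinding of acupuncturists is openly declared. The article also does not make related events by arm the safety comparison; that may be left to an analysis plan. It would therefore go too far to infer that the trial's safety result is biased. What remains is that a shared judgement with one party unblinded is not a masked judgement, and declaring a limitation does not protect the label.

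It is also fair to say that a masked rater could guess the arm from an event such as a haematoma. Masking the label is thus a partial remedy.

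**Conclusion.** The attribution point holds. As written, knowledge of the arm can enter the relatedness label. This can bias counts of treatment-related events in either arm. It leaves all-cause adverse-event counts and the nerve conduction primary outcome untouched. Its size is not computable from the document. The 1.4- to 2-fold ratios above rest entirely on assumed labelling probabilities.

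The window point holds conditionally. The documentation sentence and the week-12 end of the timed safety measures sit badly with the whole-trial statement. If the sentence is read as limiting recording to treatment, 52% to 54% of each participant's observation time may have no adverse-event recording. It is not established that this will happen.

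Together these should be corrected because safety is a stated aim and the correction is small. They do not threaten the validity of the efficacy result.

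**What to change.** 1. Have the specialists already named in the Adverse events section assign relatedness without knowing the arm. The acupuncturist supplies a description of the event and does not take part in the label. Add these specialists to the blinded roles under Masking.
2. State that the safety comparison is all adverse events by arm, regardless of attribution, with related events as a supporting display.
3. Reconcile the Adverse events section with the Abstract and Background by stating one window: adverse events are recorded from randomisation to the month-6 visit in both arms. Check that Fig. 3 agrees.

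Cost: some rewording and a few adverse-event questions at a visit that already exists. No new staff or visit is needed, and the sample size and primary analysis do not change. The downside is a longer list of unrelated background events. Some descriptions may still reveal the arm, which is why step 2 is needed as well as step 1.

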### Assessment of safety

Patients will be asked to assess safety of treatments after 12 weeks’ treatments, using a four-grade scale: safe, relatively safe, unsafe, and very unsafe.

### Sensation during the treatment

Patients will be asked about their sensation during each treatment period as following: “What sensation do you feel during the treatment? A. soreness; B. distention; C. pain; D. no feeling; E. else, please specify___.”

### Usage of medication

Medication Usage Log: Participants will be given a printed log to record their daily intake of prescribed medications. We will measure outcomes at week 12.

The schedule of enrollment, interventions, and assessments are presented in Fig. 3.

**Fig. 3 Fig3:**
[figure not shown]
The schedule of enrolment, interventions, and assessments

### Data collection, management, and monitoring

All researchers including acupuncturists, outcome assessors, and statisticians will receive training regarding data management. Case Report Forms (CRFs) will be completed and double entered into the Electronic Data Capture (EDC) system by two independent investigators to ensure accuracy of data.

All research documents, including both paper files and electronic documents, will be preserved for at least 5 years after publication. If reviewers or readers have any questions regarding our published data, they can contact the corresponding author for access to original data or visit ResMan (http://www.medresman.org/uc/project/projectadd.aspx). Private information of patients including name, telephone number, and ID number will be anonymous to ensure participant confidentiality.

Safety of this study will be monitored by a team consists of independent clinical experts and statisticians with access to unblinded data from Data and Safety Monitoring Board (DSMB) of the clinical evaluation center of Long-Hua Hospital, affiliated to Shanghai University of TCM. DSMB is independent from the sponsor, the competing interests, and the investigational site and will review the performance and safety of the trial every 6 months.

The criteria for unblinding and discontinuing allocated interventions for any trial participant experiencing serious acupuncture-related AEs have been described previously. DSMB will reveal a participant’s allocated intervention and make the final decision on whether to terminate the trial.

### Statistical methods

#### Sample size

Based on results of a previous study, a sample size of 47 participants per group was estimated to provide 80% power to detect a between-group difference of 2.4 m/s of conduction velocity improvement of common peroneal nerve, with a pooled standard deviation of 4.15 m/s and an alpha level of 0.05. The assumption of a conservative 20% drop-out rate in any group increases the sample size to 59 participants per group or 118 participants in total.

#### Statistical analysis

Statistical analysis will be performed by an independent statistician who is not aware of group allocation. SPSS 21.0 (IBM SPSS Statistics, New York, USA) will be used for data analysis. Level of significance will be established at α < 0.05 with a two-sided test. Continuous data will be represented by mean ± standard deviation or median (range), and categorical data will be represented by percentage. All efficacy analyses will be performed using the intent-to-treat (ITT) approach. For the ITT analysis, population will consist of all patients who have been randomized. Missing data will be imputed using the last observation carried forward (LOCF) method. Continuous variables will be compared using Student’s *t* test or Wilcoxon rank-sum test as appropriate. Categorical variables will be compared using Fisher’s exact test or Wilcoxon rank-sum test as appropriate. Analysis of covariance (ANCOVA) or logistic regression will be used for analysis and adjustment of baseline characteristics that differ significantly between two groups.

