### Outcomes

#### Primary outcome

The primary outcome is peroneal motor nerve conduction velocity (peroneal MNCV) which will be assessed at baseline and at week 12 after randomization.

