### Michigan Neuropathy Screening Instrument (MNSI) score

The MNSI is a clinical and semi-quantitative evaluation of neuropathy that includes medical history and physical assessment. Medical history will be completed by patients with scores ranging between 0 and 13. Physical assessment will be completed by health professionals with five indicators and the aggregate score ranging between 0 and 10: foot appearance (0 and 1 for normal and abnormal, respectively), ulceration (0 and 1 for normal and abnormal, respectively), ankle reflex (0, 0.5, and 1 for normal, reenforced, and absent, respectively), vibration test (0, 0.5, and 1 for normal, weakened, and absent, respectively), and monofilament examination (0, 0.5, and 1 for normal, weakened, and absent, respectively) of feet on both sides. The outcome measurement will be assessed at baseline, at week 12 and at month 6 after randomization.

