### Patients’ global assessment of DPN

Patients’ global assessment of DPN will be evaluated on a 5-point Likert scale at week 12. Patients will be asked to respond to the following question: “Considering all the ways your DPN affects you, how are you doing today?” 1 = very poor; 2 = poor; 3 = fair; 4 = good; or 5 = very good.

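### LOCF on a primary endpoint with one post-baseline visit enters a change of exactly 0 m/s for every patient without a week-12 MNCV, which can dilute or bias the estimated effect

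*Protocol article*

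**What the plan says.** All references are to the Protocol article; no separate SAP was available.

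- **Primary outcome:** peroneal MNCV, "which will be assessed at baseline and at week 12 after randomization". No intermediate measurement is described.
- **Statistical analysis:** efficacy is analysed by intention to treat on everyone randomised, and "Missing data will be imputed using the last observation carried forward (LOCF) method". The article names no other method for missing data. Groups are compared by t test or rank-sum test; ANCOVA is reserved for baseline characteristics that turn out to differ.
- **Sample size:** "a sample size of 47 participants per group was estimated to provide 80% power" for a difference of 2.4 m/s in improvement, "with a pooled standard deviation of 4.15 m/s and an alpha level of 0.05". Then: "The assumption of a conservative 20% drop-out rate in any group increases the sample size to 59 participants per group".
- **MNSI:** "The outcome measurement will be assessed at baseline, at week 12 and at month 6 after randomization". The Quality of life section gives the DSQL the same three visits. The Follow-up section describes three months after treatment during which acupuncture is not allowed.

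**The concern.** LOCF presupposes an earlier post-baseline value to carry forward. For MNCV there is none, so the rule becomes baseline carried forward: every patient without a week-12 MNCV is recorded as unchanged. Three things follow.

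1. The sample size treats the 20% lost as contributing nothing, leaving 47 informative patients per arm. The analysis keeps all 59 and gives those lost a zero. The analysis planned is therefore not the one that was powered.
2. If the fraction missing differs between arms while MNCV changes in both, the zeros pull the two means by different amounts. This biases the primary estimate, in a direction set by which arm loses more patients. Both conditions are plausible here. Routine care includes glucose control and neurotrophic treatment (Concurrent treatments), and only the MA arm has skin penetration and manipulation (Manual acupuncture; Sham acupuncture).
3. For MNSI and DSQL at month 6, a patient lost after week 12 keeps the end-of-treatment score. Persistence after treatment stops is then assumed for that patient rather than observed.

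**Working it through.** **Inputs from the plan:** difference 2.4 m/s, SD 4.15 m/s, alpha 0.05 ("with a two-sided test"), power 80%, 1:1 allocation, 20% loss, 59 per arm.

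**Assumptions of this check:** 4.15 is the SD of change (the plan does not say, but it describes the difference as one of improvement); all loss falls before week 12; patients lost would have responded like completers. The mean sham change is not given, so a range is shown.

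**Step 1. Reproduce the plan.** n = 2 × [4.15 × (1.960 + 0.842) / 2.4]² = 46.9, so 47 per arm. 47 / 0.8 = 58.75, so 59 per arm and 118 in total. Both figures reproduce. Power at 47 per arm is 80.1% by the normal formula and 79.2% by the t test.

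**Step 2. Distribution under LOCF.** With a fraction d set to zero and the rest having mean μ and SD σ:

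- mean = (1 − d)μ
- variance = (1 − d)σ² + d(1 − d)μ²

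**Step 3. Equal 20% loss.** The expected difference is 0.8 × 2.4 = 1.92 m/s for any sham change. With no sham change the variances are 0.8 × 4.15² + 0.16 × 2.4² = 14.70 (MA) and 0.8 × 4.15² = 13.78 (SA). The pooled SD is √[(14.70 + 13.78)/2] = 3.77, the standard error 3.77 × √(2/59) = 0.695, and the ratio 1.92 / 0.695 = 2.76.

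| Mean sham change (assumed) | Difference under LOCF | Pooled SD | Power, t test, 59 per arm |
|---|---|---|---|
| 0 m/s | 1.92 | 3.77 | 78% |
| 2 m/s | 1.92 | 3.96 | 74% |
| 5 m/s | 1.92 | 4.49 | 63% |

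The normal approximation gives 79%, 75% and 64%. The comparison is 79% for 47 completers by t test.

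**Step 4. Unequal loss, no true effect.** With a common change m, the spurious difference is (d₂ − d₁) × m. Type I error is Φ(δ/se − 1.96) + Φ(−δ/se − 1.96), where δ is the spurious difference and se = √[(v₁ + v₂)/59], with v from Step 2. For m = 3 m/s:

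- 10% vs 20% missing: δ = 0.1 × 3 = 0.3 m/s; se = √[(16.31 + 15.22)/59] = 0.731; δ/se = 0.41; type I error about 7%.
- 10% vs 30% missing: δ = 0.2 × 3 = 0.6 m/s; se = √[(16.31 + 13.95)/59] = 0.716; δ/se = 0.84; type I error about 13%.

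For 10% vs 30% with a smaller common change, m = 1 gives 0.2 m/s (about 6%) and m = 2 gives 0.4 m/s (about 9%).

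**Step 5. Unequal loss, true effect 2.4 m/s, sham change 2 m/s.**

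- 20% missing in MA, 10% in SA: 0.8 × 4.4 − 0.9 × 2 = 1.72 m/s.
- 10% missing in MA, 20% in SA: 0.9 × 4.4 − 0.8 × 2 = 2.36 m/s.

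The same true effect gives estimates 0.64 m/s apart, depending only on which arm loses more patients.

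**The case against.** **Power.** A reader might infer that LOCF destroys the stated 80% power. The plan's own figures do not support that. The imputed zeros reduce the SD from 4.15 to 3.77 while they dilute the difference, and the analysis keeps 59 rather than 47 per arm. With no sham change the cost is about one percentage point. Larger losses need a sham improvement that the plan does not state. This objection stands.

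**Who is affected.** Not every dropout gets a zero. Someone lost between week 12 and month 6 already has a week-12 MNCV. The plan's 20% is not tied to week 12, so applying all of it to the primary endpoint is an upper-end reading. This stands too.

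**False positives.** With equal missingness and no true effect, both arms have the same mixture distribution, so the comparison stays unbiased. Inflation requires unequal missingness together with a common change. The 30% scenario exceeds the loss that the plan calls conservative, and 3 m/s exceeds the target effect; milder inputs give milder inflation (Step 4). These are illustrations of the mechanism, not forecasts.

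**Month 6.** LOCF need not overstate durability. It does so for patients lost after week 12 only if benefit wanes, and a patient missing both visits gets the baseline score, which understates any benefit.

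**Omissions.** The patients' global assessment "will be evaluated on a 5-point Likert scale at week 12" leaves nothing to carry forward, but its handling is ordinary SAP detail, as are further sensitivity analyses. Neither is counted here.

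None of this rescues the rule for the primary endpoint. The article fixes it explicitly, and its effect on MNCV follows directly from the visit schedule.

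**Conclusion.** The point holds as one about dilution and bias. Every randomised patient without a week-12 MNCV is analysed with a change of exactly 0 m/s; that part needs no outside assumption.

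The size is conditional. The fall from 2.40 to 1.92 m/s assumes the full 20% loss occurs before week 12 in both arms, among patients who would have responded like completers. The spurious differences of 0.3 and 0.6 m/s assume unequal missingness and a common improvement of 3 m/s. Power is a secondary matter: about 78% on the plan's inputs, lower only with assumed sham improvement. For MNSI and DSQL at month 6, persistence is assumed for patients lost after treatment, which overstates durability if benefit wanes.

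This deserves correction because LOCF is the only missing-data rule the article states for its single primary endpoint, in a trial that itself plans for 20% loss.

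**What to change.** Before unblinding, amend the Statistical analysis section as follows.

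- **Primary endpoint:** replace LOCF with a baseline-adjusted ANCOVA of week-12 MNCV in all randomised patients, valid under missing at random, using multiple imputation by arm from baseline data already collected (for example baseline MNCV and HbA1c).
- **MNSI and DSQL:** use a mixed model for repeated measures over week 12 and month 6, so that a missing month-6 score is not replaced by the end-of-treatment value.
- **LOCF:** keep at most as a sensitivity analysis.

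The cost is a wording change and slightly more programming; no extra patients or visits are needed. The Masking section keeps allocation hidden until the analysis is complete, and Trial status reports recruitment as still open, so on the article's account the change can be made blind. The downside is reliance on missing at random, which the data cannot verify. With only one post-baseline MNCV, imputation recovers little information about the patients lost; the gain is that they are no longer recorded as unchanged.
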